## Abstract

**Background:**

The rapid response system (RRS) is a process of accessing help for health professionals when a patient under their care becomes severely ill. Recent studies and meta-analyses show a reduction in cardiac arrests by a one-third in hospitals that have introduced a rapid response team, although the effect on overall hospital mortality is less clear. It has been suggested that the difficulty in establishing the benefit of the RRS has been due to implementation difficulties and a reluctance of clinical staff to call for additional help. This assertion is supported by the observation that patients continue to have poor outcomes in our institution despite an established RRS being available. In many of these cases, the patient is often unstable for many hours or days without help being sought. These poor outcomes are often discovered in an ad hoc fashion, and the real numbers of patients who may benefit from the RRS is currently unknown. This study has been designed to answer three key questions to improve the RRS: estimate the scope of the problem in terms of numbers of patients requiring activation of the RRS; determine cognitive and socio-cultural barriers to calling the Rapid Response Team; and design and implement solutions to address the effectiveness of the RRS.

**Methods:**

The extent of the problem will be addressed by establishing the incidence of patients who meet abnormal physiological criteria, as determined from a point prevalence investigation conducted across four hospitals. Follow-up review will determine if these patients subsequently require intensive care unit or critical care intervention. This study will be grounded in both cognitive and socio-cultural theoretical frameworks. The cognitive model of situation awareness will be used to determine psychological barriers to RRS activation, and socio-cultural models of interprofessional practice will be triangulated to inform further investigation. A multi-modal approach will be taken using reviews of clinical notes, structured interviews, and focus groups. Interventions will be designed using a human factors analysis approach. Ongoing surveillance of adverse outcomes and surveys of the safety climate in the clinical areas piloting the interventions will occur before and after implementation.

## Background

Patients that become critically unwell in a hospital ward environment commonly exhibit a recognisable period of abnormal physiological signs before they suffer a cardiac arrest or other catastrophic event [1-6]. It has been established that early intervention may halt their deterioration and prevent a cardiac arrest or unplanned intensive care unit (ICU) admission. The rapid response system (RRS) is a process whereby health professionals can promptly access help if a patient under their care deteriorates and before they become critically ill to prevent further instability. The type of assistance varies depending on the setting, but typically the medical emergency team (MET) that responds consists of trained specialist staff members such as intensivists and senior nurses.

Many studies [7-9] and a recent meta-analysis [10] showed that the number of cardiac arrests in hospitals can be reduced by the introduction of a RRS. The MERIT study [11], the only multicentre prospective randomised study, initially showed no benefit. A recent *post hoc *analysis of the MERIT data of both intervention and control hospitals, however, demonstrated early intervention using a RRS clearly reduces in-hospital cardiac arrests and mortality [12].

The difficulty in establishing the effectiveness of RRSs and METs has at least in part been due to the failure of clinical staff to call for help early in all circumstances. A review of critical incidents in our own institution, suggested that a failure to call the MET was a common factor in a large proportion of cardiac arrests and unplanned ICU admissions [13]. The reasons behind this failure to call for help have not previously been investigated.

### Failure to activate the RRS

In order to help health professionals to identify when a patient is becoming physiologically unstable, specific criteria based on the vital signs are often fixed for use at the point of care. Deviation outside of these physiological criteria such as those listed in Table 1 represent a state where the patient is thought to be at an increased risk of further deterioration, or has a limited reserve to cope with additional physiological insults [1].

**Table 1 T1:** Medical emergency team call criteria or triggers

Airway	Respiratory Distress Threatened Airway
Breathing	Respiratory Rate > 30 breaths per minute Respiratory Rate < 6 breaths per minute Oxygen Saturation <90% on oxygen

Circulation	Blood Pressure < 90 mmHg despite treatment Pulse Rate > 130 beats per minute

Neurology	Decreased level of consciousness Fitting

Other	Concerned Need of treatment & prompt help

It is currently unclear how many patients in a routine ward environment would meet the abnormal physiological criteria, or if they would progress to an unstable state and benefit from activation of the RRS. Defining the subgroup of patients who would probably have benefitted from early intervention would allow the underlying factors to be more readily investigated and addressed by redesigning of the process and more targeted education for the staff.

Several barriers have already been identified in the literature that prevent the initial implementation of a RRS; failure to view errors as a product on the system rather than individual mistakes, lack of data that METs are life saving, professional control issues, effective education, and financial pressures [14]. It is possible the barriers to ongoing effectiveness are similar, but these have not been identified in the literature. We hypothesise that further barriers exist to prevent the staff members calling for help. These involve both the individual health professionals' internal cognitive processes and cultural expectations from the clinical context and professional identities.

### Theoretical framework

As noted above, no single theory is available to describe why, when patients meet defined criteria, that the staff members do not activate the RRS. We will employ theoretical triangulation [15] using theories from the cognitive engineering model of situation awareness, and sociologically informed models of inter-professional practice [16] to aid further investigation (Figure 1). Both of these theories will be applied in parallel to develop a detailed understanding of the psychosocial process of RRS activation.

**Figure 1 F1:**
[figure not shown]
A theoretical framework describing the cognitive and socio-cultural barriers to calling the Medical Emergency Team (MET)

### Situation awareness

Situation awareness describes the gathering and understanding of cues in the environment leading to a projection of the possible future consequences [17]. In the circumstance of a deteriorating patient, each health professional makes his or her own assessment of the situation and decides on a resultant course of action, perhaps in consultation with colleagues. The situation awareness model has three distinct parts: perception, comprehension, and projection.

### Perception

Perception of the vital signs of a deteriorating patient typically means that the observations have been taken and transposed to the observation chart. If the patient is deemed to be unwell, these observations will usually be repeated more frequently to ensure that a further deterioration is not occurring and that treatment is effective.

### Comprehension

Comprehension of the meaning of the physiological signs is also important. Specifically with the RRS, the clinical staff must be able to recognise how the patient's observations relate to the triggering criteria. A deeper level of comprehension of the patient's physiological state may occur with more experienced staff members. This may lead to a recollection and comparison to past experiences of similar cases to guide future decision making and information gathering [18]

### Projection of future state

The ability of the health professional to project the future course of events is determined by an understanding of the current state and their previous experiences with similar situations. The rationale given for the clinical staffs' predictions may not always be obvious, even to them. This 'sixth sense' of being able to project the future state is often the result of cues that may not be consciously recognised [19]. One of the advantages of the RRS is that it removes the necessity of the clinical staff to fully understand and diagnose the problem before asking for help. If the health professional looking after the patient is confident they know what the clinical problem is, they may be able to troubleshoot the problem without requiring help. Conversely, if the health professional is junior with only minimal experience, the triggering criteria should trigger them to call for assistance.

### Sociological models of inter-professional practice

Even if the health professional realises the patient fulfils the physiological criteria for activation of the RRS, there may be socio-cultural and political barriers preventing them from calling for help. These barriers may occur between professional groups, within professional groups, or as a result of a group identity existing such as within a ward or specialty area.

### Inter-professional barriers

Barriers may occur at an inter-professional level where there are perceived to be differing levels of trust and cooperation between professional groups [20]. The RRS may be prevented from being activated by levels of distrust between the emergency team attending and the treating groups. Similarly, barriers may be occurring because of the differing views and perceived role of the RRS by nursing and medical staff.

### Intra-professional barriers

Pre-existing pathways to activating the RRS may be based in the culture of the profession [21]. It has been established that nursing staff are more likely to activate the RRS than medical staff [22]. This difference between professional groups could be a result of cultural barriers within the medical profession that have not previously been identified.

### Contextual and local cultural factors

Specific clinical areas of the institution may exhibit differing cultures about the role and function of the MET and pathways to access help. These clinical areas are in turn situated within the complexity of the character of the institution itself. One of the many potential factors that has already been identified in supporting a RRS is whether the hospital has a teaching function [23]. Other local cultural aspects have not been investigated, such as the presence of implicit or explicit directions to seek help from other sources before activating the RRS, which may vary between clinical areas.

The experiences of individuals' interpersonal interactions during MET calls also may have a detrimental effect on future optimal MET call behaviour amongst staff. For example, the attitude of the MET call team on their arrival may have a substantial effect on the culture of the clinical area. If the team is negative and critical, the ward staff may be reluctant to call for help on future occasions, whereas a helpful team that supports and educates the staff will encourage a positive attitude [24].

### Aims of this study

The aims of the proposed study are threefold: to establish the scope of the problem; to examine the barriers to calling the MET; and to pilot a redesign of the RRS to improve its effectiveness.

### Establishing the scope of the problem

First, we intend to determine the prevalence of patients meeting the physiological criteria for activation of the RRS at a number of hospitals. We will identify the number of patients who would have benefited from early intervention but didn't receive it. This will allow a further measure to be developed: the 'missed MET', which will be useful in examining the barriers to calling the MET.

### Examining the barriers to calling the MET

The reasons why the RRS was not activated by ward staff will be determined using the theoretical framework described in figure 1. Health professionals will be approached from all groups involved in RRS activation, from junior and senior medical and nursing staff, to members of the MET themselves to ascertain the common reasons why help may not be called, or called too late. Staff involved in successful and unsuccessful rapid response events will be approached as well as those involved in cases of 'missed MET'.

### Redesigning the MET system

In any knowledge translation activity, it is essential that the end users of the knowledge are included to ensure that the knowledge and its subsequent implementation are relevant to their needs [25]. Once the scope and barriers to the RRS are understood, we will pilot a redesign of the RRS to increase its effectiveness. Evaluation of these interventions will be determined by repeat measurements from the first two phases of the study (Figure 2).

**Figure 2 F2:**
[figure not shown]
Overview of methods to be used

## Methods

Three related studies will be undertaken concurrently with data collected before and after the design and implementation of an intervention to address the issues identified (Figure 2).

### Point prevalence study

The prevalence of patients meeting the physiological criteria for MET calls will be measured across four hospitals of differing size and caseload over a 24-hour period. These hospitals include an outer suburban 520 bed acute hospital, a small 120 bed elective surgical and oncology centre, a large metropolitan teaching hospital, and an outer suburban community hospital. These four hospitals comprise the majority of the acute care of a health network with over 12,000 staff, 2,100 beds and 180,000 hospital admissions. A team of researchers will examine the clinical notes of all adult in-patients that are not being cared for in critical care areas (ICU, emergency department, or operating theatres). The clinical staff involved with those patients at the time the criteria were attained will be interviewed to determine why a MET call had not been made. Data collected from these structured interviews will be used due to the time constraints of the study and potential to interrupt clinical work. The interview questions will be based on the theoretical framework given in Figure 1. All of the patients identified will be followed up to discharge from hospital to determine if the rate of adverse outcomes in patients meeting the physiological criteria. Particular note will be made to determine if any of these patients subsequently became critically ill, require ICU admission or a cardiac arrest call.

This point prevalence study will be the main study determining the scope of the problem, and to define the 'missed MET' for future study. The data collected from the interviews are expected to be sketchy in terms of determining barriers to the MET call due to the limited time available, but may inform the direction of later phases.

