### Prospective audit

Analysis of all unplanned ICU admissions and cardiac arrests will be performed over an eight-week period before the intervention and an eight-week period three months following implementation of the interventions across all four hospitals in the study.

The clinical notes of all unplanned ICU admissions and cardiac arrests will be examined for evidence of a 'missed MET' in the preceding hours or days. This will determine if an early intervention may have prevented the patient becoming critically ill. Clinical staff involved in the care of a patient that has a 'missed MET' will be interviewed using the same structured interview used in the point prevalence study.

The prospective audit will further allow the barriers to the MET call to be determined from actual cases. Furthermore, the incidence of 'missed MET' will be able to be determined.

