### Intervention design

Adapting knowledge to the local context is a crucial component in the knowledge translation process [25]. Up to six common barriers identified from the point prevalence, focus group, interview, and prospective case methods will be determined. These barriers will be presented at a workshop consisting of up to twenty clinical staff involved in the MET call process. Case studies will be used to illustrate how the barriers contribute to 'missed MET' calls, and the participants in the workshop will be asked to provide solutions. The potential solutions will then be categorised using the Human Factors Analysis and Classification System (HFACS), and solutions developed using the Human Factors Intervention Matrix (HFIX) [28]. These potential solutions will be rated in terms of feasibility, acceptability, cost effectiveness, effectiveness, and sustainability. Up to five solutions will be chosen, and be implemented as part of the redesign process. The effects of each individual intervention will not be assessed separately.

Six clinical areas will be chosen from the four hospital sites to introduce the redesigned MET system. These six areas will also have additional point prevalence surveys to determine if the mechanism for dealing with the physiologically unstable patient has changed after introduction of the new system. A further prospective audit will also be used to assess the effectiveness of the redesigned solution.

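### Vital-sign triggers and missed METs are read only from the notes, so prevalence can be understated, and before/after counts can shift if the redesign changes how often observations are made

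*Protocol article*

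**What the plan says.** All references are to the protocol article.

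- **Point prevalence study.** The target is stated as "The prevalence of patients meeting the physiological criteria for MET calls will be measured across four hospitals" over 24 hours. The data source is the record: "A team of researchers will examine the clinical notes of all adult in-patients", limited to those "that are not being cared for in critical care areas". No measurement of vital signs by the researchers is described. Interviews start from the patients so identified: "The clinical staff involved with those patients at the time the criteria were attained will be interviewed".
- **Prospective audit.** The notes of all unplanned ICU admissions and cardiac arrests "will be examined for evidence of a 'missed MET' in the preceding hours or days". Staff are interviewed where one is found.
- **Perception.** The first stage of the situation-awareness model is described thus: "Perception of the vital signs of a deteriorating patient typically means that the observations have been taken and transposed to the observation chart". The section adds that observations are usually repeated more often once a patient is judged unwell.
- **Redesigning the MET system; Intervention design.** The interventions are evaluated by repeating the measurements of the first two phases. The six pilot areas have further point prevalence surveys "to determine if the mechanism for dealing with the physiologically unstable patient has changed after introduction of the new system", and there is a further audit.

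**The concern.** The survey's denominator is every eligible ward in-patient. Its numerator is every patient with a criterion visible in the notes. For respiratory rate, saturation, blood pressure and pulse (Table 1), a criterion is visible only if the observation was made and written down. A patient who was not observed is therefore counted with the patients who were observed and found stable.

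This matters here more than in most chart reviews, because making and charting observations is itself a stage at which the protocol expects the system to fail. The case-finding method mostly finds patients for whom that stage succeeded. Three things follow:

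- the scope of the problem can be understated, most where observation is poorest;
- the case-based interviews will seldom reach staff involved in a perception failure;
- if a chosen solution alters how often observations are made, the before/after prevalence and missed-MET count can change for that reason alone.

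**Working it through.** The article gives no expected prevalence, charting completeness or call rate, so there is no figure of its own to reproduce. Every input below is an assumption made to show direction and size. The observation intervals are illustrative and are not a recommendation.

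**Model.** Let p be the true prevalence of triggers, c the share of triggers that are charted, and k the share of charted triggers followed by a call. Subscripts 0 and 1 mean before and after. Uncharted triggers are taken to lead to no call.

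- Apparent prevalence = p × c
- Counted missed METs = p × c × (1 − k)
- All uncalled triggers = p × (1 − c × k)
- With p unchanged, counted missed METs rise only if c1(1 − k1) > c0(1 − k0). The break-even call share is k1 = 1 − (c0/c1)(1 − k0).

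**Illustration by episode length.** Assume 1,000 patients with 100 true episodes, observations moving from 8-hourly to 4-hourly, and k rising from 0.40 to 0.50. Take c = episode length / observation interval, capped at 1.

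| Episode | c before → after | Charted | Counted missed METs | All uncalled | Break-even k1 |
|---|---|---|---|---|---|
| 2 h | 0.25 → 0.50 | 25 → 50 | 25 × 0.6 = 15 → 50 × 0.5 = 25 (+67%) | 90 → 75 | 0.70 |
| 6 h | 0.75 → 1 | 75 → 100 | 75 × 0.6 = 45 → 100 × 0.5 = 50 (+11%) | 70 → 50 | 0.55 |
| 8 h or more | 1 → 1 | 100 → 100 | 100 × 0.6 = 60 → 100 × 0.5 = 50 (−17%) | 60 → 50 | 0.40 |

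For episodes between 4 and 8 hours (length L), the count before is 100 × (L/8) × 0.6 = 7.5L and the count after is 50. They are equal at L = 50/7.5, about 6.7 h. Below that length the count rises although calling has improved; above it the count falls.

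Apparent prevalence goes from 2.5% to 5.0%, from 7.5% to 10%, and stays at 10% in the three rows. True prevalence is 10% throughout.

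**Check without the interval formula.** Take p = 5%, with c rising from 0.60 to 0.90.

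- Apparent prevalence: 3.0% → 4.5%, a ratio of 0.90/0.60 = 1.5 at any p.
- With k steady at 0.30, counted missed METs per 100 patients: 5 × 0.60 × 0.70 = 2.10 → 5 × 0.90 × 0.70 = 3.15.
- All uncalled triggers per 100: 5 × (1 − 0.18) = 4.10 → 5 × (1 − 0.27) = 3.65. The count moves the opposite way to the true shortfall.
- Break-even k1 = 1 − (0.60/0.90) × 0.70 = 0.533. At k1 = 0.60 the count falls to 5 × 0.90 × 0.40 = 1.80.
- With c0 from 0.50 to 0.80 and c1 = 0.90, the prevalence ratio runs from 1.80 to 1.125. True prevalence would have to fall by 44% to 11% to hide it.

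**What is stable.** The share of charted triggers with a call is k. In this model it does not depend on c: it goes from 40% to 50% in every row of the table.

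**The case against.** The case on the other side is substantial, and much of it stands.

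- **Long episodes.** The Abstract says that patients with poor outcomes are often unstable for many hours or days. At 8 hours or more the illustration shows no detection artefact and the count falls as it should. That statement concerns poor-outcome cases, not all triggers, so shorter episodes remain possible.
- **The redesign does not yet exist.** Solutions come from a workshop, and nothing says they will alter observation. A reader might infer that a better system will be made to look worse. The documents support only that it can.
- **Scoring.** A reader might also infer that an arrest with no preceding observations is scored as no failure. No such rule is written. The survey is still to define the missed MET, and the coding of absent observations may sit in a fuller document.
- **Success criterion.** No raw count is named as the test of success. The stated purpose of the repeat surveys, how unstable patients are dealt with, is close to a proportion called.
- **Other triggers.** Fitting, a threatened airway, respiratory distress or staff concern can appear as free text.
- **Other sources on barriers.** Focus groups, and staff from successful and unsuccessful events, also contribute, so perception failures are not wholly out of reach. The focus groups are, however, directed at socio-cultural factors.

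None of this changes the stated data source, the all-patient denominator or the reuse of the same measures before and after.

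**Conclusion.** The point holds in a conditional form. Because the notes are the only stated source, prevalence of vital-sign triggers can be understated, and perception failures are hard to see in the case-based interviews. If observation frequency changes between periods, prevalence and the missed-MET count can shift with it.

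Under the assumed inputs the change in the missed-MET count runs from +67% for 2-hour episodes to −17% for episodes of 8 hours or more, with the sign turning at about 6.7 hours. These figures rest on the assumed intervals, call shares and a simple detection rule, none of which comes from the article.

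A reader might extend the criticism to the whole audit. That would be wrong: unplanned ICU admissions and cardiac arrests are found by the event, so their counts are unaffected. Only their classification as preceded by a missed MET is exposed.

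**What to change.** In both periods, and from the notes already being read:

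1. Abstract the number and times of observation sets for each surveyed patient and each audit case.
2. Report a class for observations absent or insufficient (not assessable), separate from criteria not met in the survey and from no missed MET in the audit.
3. Compare before and after on the proportion of charted-trigger patients who had a MET call, shown beside observation completeness. Do not rely on raw counts alone.

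The cost is extra abstraction fields and a published not-assessable fraction. The proportion is not perfectly protected: closer observation may pick up briefer episodes with a different chance of a call, which is why completeness must be shown with it.

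Extending the structured interviews to staff of every patient with overdue observations is not part of this fix. The Point prevalence study section already cites limited time and possible interruption of clinical work.

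### The point prevalence interview may prompt help for patients still meeting criteria, and the same patients' outcomes are then followed without separating what came before and after that contact

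*Protocol article*

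**What the plan says.** All references are to the protocol article.

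- **Methods, Point prevalence study.** The prevalence of patients meeting the call criteria "will be measured across four hospitals of differing size and caseload over a 24-hour period". Researchers read the notes of adult in-patients outside critical care areas. The staff who were looking after a patient when the criteria were reached "will be interviewed to determine why a MET call had not been made".
- **Same section, format of the interview.** Structured interviews are chosen "due to the time constraints of the study and potential to interrupt clinical work", and the information on barriers is "expected to be sketchy in terms of determining barriers to the MET call due to the limited time available".
- **Same section, follow-up.** "All of the patients identified will be followed up to discharge from hospital", with attention to later critical illness, ICU admission and cardiac arrest calls. This component is named as the main source for the scope of the problem and for defining the missed MET.
- **Aims, Establishing the scope of the problem.** The first aim includes identifying "the number of patients who would have benefited from early intervention" and did not get it.
- **Methods, Intervention design.** Six clinical areas have further point prevalence surveys after the redesign, to see whether unstable patients are handled differently.

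**The concern.** One set of patients serves two purposes. They trigger a conversation with the people who can make the call, and they supply the outcomes that describe what follows once criteria are met. Asking a nurse or doctor why no call was made tells them that one was due. If the patient is still unstable, that may be enough to bring help.

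The outcomes to discharge would then mix patients left to the ward's usual course with patients whose course was changed by the survey. The article describes nothing that would tell the two apart. At stake is the adverse-outcome rate that informs the scope estimate and the missed-MET definition. The repeat surveys have a second exposure. If staff are interviewed there too, a call made because a researcher asked could be counted as the redesign working.

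**Working it through.** The article gives no event rate, sample size or effect size on this point, so there is no figure of its own to reproduce. The check is a reading of the text followed by an illustrative calculation.

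**1. When is the interview?** No time is stated. Two phrases bear on it: the concern about interrupting clinical work and the limited time available. Both fit interviews on the ward during the survey. Neither places the interview while the patient is unstable, and the pluperfect in "will be interviewed to determine why a MET call had not been made" fits an interview after the episode equally well. Overlap is therefore possible and not established.

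**2. Which quantities can the interview change?**

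| Quantity | Can the interview change it? |
|---|---|
| Prevalence of criteria met before contact | No, already in the notes |
| Absence of a call before the interview | No, this is what triggers the interview |
| Outcomes to discharge, episode over before contact | Not by prompting help for that episode |
| Outcomes to discharge, episode open and uncalled at contact | Yes |
| Index ICU admissions and arrests in the prospective audit | No, they precede the audit's interviews |

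**3. How large could the effect be?** Inputs, all assumed:

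- *p*: the adverse-outcome rate without prompting. It cancels.
- *f*: the share of followed patients for whom the interview brings help.
- *RR*: the relative risk of an adverse outcome with that help. The middle value, 2/3, borrows the one-third reduction in cardiac arrests in the abstract. That figure is at hospital level and for arrests only, so using it per patient and for a wider set of outcomes is an assumption.

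Observed rate = (1 − f) × p + f × RR × p, so

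observed / unprompted = 1 − f × (1 − RR).

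At RR = 2/3 and f = 10%: 1 − 0.10 × 0.333 = 0.967. At f = 100%: 1 − 0.333 = 0.667. The full range is:

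| RR | f = 0 | f = 10% | f = 25% | f = 50% | f = 100% |
|---|---|---|---|---|---|
| 0.9 | 100% | 99.0% | 97.5% | 95.0% | 90.0% |
| 2/3 | 100% | 96.7% | 91.7% | 83.3% | 66.7% |
| 0.5 | 100% | 95.0% | 87.5% | 75.0% | 50.0% |

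The formula takes prompted and unprompted patients to have the same underlying risk. If open episodes carry more risk, the share of events affected exceeds the share of patients, and the attenuation is greater than shown.

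**4. Is the direction fixed?** No. ICU admission is one of the outcomes, and a prompted review may itself lead to one. For that component RR could exceed 1, and the same formula then gives a ratio above 1.

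**The case against.** **The timing is inferred.** This stands. The point can only be put conditionally.

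**The abstract's remark on duration does not settle it.** A reader might cite "the patient is often unstable for many hours or days without help being sought" to argue that many surveyed patients will still be unstable when staff are approached. That sentence describes patients who came to notice through poor outcomes. It does not describe everyone who meets a criterion on a survey day, and the section on failure to activate the RRS says it is unclear whether such patients progress. It shows that long episodes occur, not how common they are here.

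**The follow-up covers everyone identified.** A reader might take it as a cohort of unhelped patients. The article follows all patients meeting criteria, some of whom may receive help anyway. This also stands: the overall rate among them was never a pure untreated course. It remains true that help brought by the survey is a different thing from help brought by usual care.

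**Misclassification of missed METs.** A reader might infer that a prompted call turns a missed case into a called one. The absence of a call is known before staff are questioned, so this could happen only if status were scored after contact, which the article does not say.

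**An article leaves such detail to the full protocol.** This has force for time stamps and coding. It does not dispose of the point, because the article does set out the two uses of the same patients, and contact times not captured on the day cannot be recovered in the analysis.

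**Conclusion.** The point holds in a limited form. As described, the interview can alter the followed-up outcomes of any patient who still meets criteria and is uncalled when staff are questioned, and nothing described separates those patients from the rest. Under the stated assumptions, with RR = 2/3, the observed rate lies between 66.7% and 100% of the unprompted rate, and is 96.7% if one patient in ten is prompted. These figures illustrate and do not estimate: *f* is unknown, and RR rests on a borrowed hospital-level figure.

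A reader might infer that the survey necessarily prompts the missing help, that the follow-up no longer shows the course without it, or that harm is certainly understated. The documents support none of these. The interview time is not given, only open and uncalled episodes are exposed, and prompted review could raise ICU admissions. What remains is a possible contamination of unknown size and uncertain direction in one measure. It is worth correcting because the remedy is cheap and is available only during data collection.

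**What to change.** In the point prevalence procedure:

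1. Abstract the notes before speaking to ward staff.
2. For each identified patient, record the time of first researcher contact with staff and whether criteria were still met then.
3. Fix missed-MET status at that time.
4. Record the time of any later MET call or escalation and code it as after survey contact. The code marks sequence; it does not prove that the survey caused the call.
5. Report adverse outcomes for all identified patients, and separately for episodes closed and open at contact. State that the closed group is smaller and selected, since those episodes ended before anyone asked.
6. Use the same coding in the repeat surveys on the six pilot areas, so that a call following researcher contact is not read as an effect of the redesign.

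The cost is two time stamps and one code per identified patient, plus the discipline of reading notes first. The price in precision is that the estimate least exposed to prompting rests on fewer patients.
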